### Statistical analysis

In the three recruitment areas of the cohort study (Berlin, Leipzig and Flensburg) almost 49,000 children have been born annually in recent years. A random sample of 30,000 children is drawn by the residents' registration offices, and their parents are invited to take part in the study. The response is estimated to be 20%; therefore, about 6000 mother–child pairs are expected to participate in the study. Assuming a prevalence of mental health problems in postnatal mothers of about 20% [8], a similar prevalence of regulatory problems in their children [68] and a considerable overlap of both problems, about 1,500 of the estimated 6,000 mother–child-pairs are expected to be included into the screening step 2 (Fig. 1). In the screening step 2, we estimate that about 1,200 participating mother–child-pairs with maternal mental health disorders and/or symptoms of regulatory problems in the child will be identified. For an occurrence of 20% of mental health disorders (1200 of 6000), a two-sided exact Clopper-Pearson 95%-confidence interval (95% CI) of 6000 participants has a width of ± 1% (i.e., 95% CI [19%; 21%]). This is considered sufficiently precise.

All data will be analysed descriptively. Results are presented in the form of means, standard deviations, medians and quartiles for continuous data, and frequencies and percentages for categorical data. Results (including occurrences) are reported with two-sided 95% CIs. Influencing factors for the presence of psychosocial stress or mental health disorders are analysed using logistic regression yielding odds ratios (OR) with 95% CIs and *p* values. Influencing factors or group comparisons for continuous variables (e.g. costs) will be analysed by linear regression or analysis of covariance (ANCOVA), yielding regression coefficients or means with 95% CIs and *p* values. All CIs and *p* values are two-sided and are interpreted exploratively (there is no formal significance level). Missing values are not replaced. All analyses are carried out with the respective available data (full analysis set).

For the cost analysis, the monetary valuation of the utilization of services is carried out by multiplying the frequency of utilization and corresponding standardized cost rates.

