### Endpoints

The primary endpoints of the cohort study are:i.*For mothers*: (i) presence of at least one current mental health disorder (based on the M.I.N.I interview [59]). (ii) presence of parental burnout symptoms (defined as score of ≥ 76 in the Parental Burnout Assessment questionnaire [12]). (iii) Presence of depressive symptoms (defined as an Edinburgh Postnatal Depression Scale (EPDS) score of 10–12 points (minor symptoms) or ≥ 13 points (major symptoms) versus 0–9 points (no symptoms) [5]ii.*For children*: presence of problems concerning crying, feeding and sleeping (so-called regulatory problems) (defined as a total score of ≥ 1.85 in the questionnaire on crying, feeding and sleeping disorders [60]). Subscales (crying, feeding and sleeping) will also be evaluated individually.

Secondary endpoints include:*For mothers*: presence of the following current mental health disorders: major depressive episode, major depressive disorder, manic and hypomanic episodes, panic disorder, agoraphobia, social anxiety disorder (social phobia), obsessive–compulsive disorder, posttraumatic stress disorder, alcohol use disorder, substance use disorder (non-alcohol), Anorexia nervosa, Bulimia nervosa, binge-eating disorder, generalized anxiety disorders.*For mothers and children*: health care and social services utilisation and costs: medical consultations, utilisation of midwifery care/physical therapy/speech therapy/occupational therapy, acute and rehabilitation hospital stays, utilisation of Early Childhood Intervention program components etc..

Additionally, the course and patterns of the observed disorders and problems will be evaluated by a follow-up assessment after 6 months. Potential risk and protective factors such as sociodemographic characteristics, marital, family, health, and work related stressors, critical life events, and pre-existing mental health disorders will be examined. If fathers agree to participate in the screening step 1, we will have the information of the latter also for the fathers.

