### Instruments

#### Screening step 1

In the screening step 1, study participants fill out a short online-questionnaire. The questionnaire was developed with the aim of having a high sensitivity to detect potential mental health disorders and psychosocial stress. By implementing a two-step screening design we hope to reach a high sensitivity and high specificity, allowing an accurate early detection of stress or mental health problems in parents and their children. There are existing screening instruments like the Babylotse-Plus screening form [61] or the Heidelberg Stress scale [62], but they showed either a high sensitivity and low specificity [61] or only a moderate sensitivity [62].

The questionnaire for the screening step 1 (self-developed and adapted parts) contains questions regarding the parent’s health status: symptoms of depression and/or anxiety, obsessive–compulsive problems, abuse/addiction to alcohol/drugs, eating problems, lack of impulse control or mood swings, pre-existing mental health disorders. Questions regarding the child include the assessment of signs of crying, sleeping or feeding problems.

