In addition, questions on sociodemographic characteristics, stress related to relationships, family and work, lack of social support and critical life events related to the pregnancy and child (for example an unplanned pregnancy or severe illness of the child) will be assessed. To reduce selection bias, the questionnaire was kept as long as necessary but as short as possible and in simple language, to achieve a high participation rate especially in those with a lower educational level or non-native German speakers. Otherwise, particularly those at risk for psychosocial stress and mental health disorders might be under-represented in the study. Therefore, either short questionnaires such as the Patient Health Questionnaire 4 [63] or individual questions from existing questionnaires were selected or adapted (the Crying, Feeding, Sleeping Questionnaire [60], the Zohar-Fineberg Obsessive Compulsive Screen [64], the Postpartum Bonding questionnaire [65], and the KID 0–3 questionnaire [66]). We developed a scoring system with points ranging from 0–5 for each question. The scores were discussed with a panel of experts from psychology, paediatrics, health sciences, and data sciences, taken into account cut-offs of included questionnaires. We piloted the questionnaire and adapted it as indicated (e.g. adding or rewording of response options). The scope of this pilot study was to test if the questionnaire was comprehensible, appropriate and feasible for the participants. Cut-offs were defined consensus based in order to identify a maximum of mothers with possible disorders, but the data from pilot study did not allow to conduct an in-depth analysis to calculate sensitivity or specificity. All mothers with an elevated score are invited to the screening step 2. This score was adjusted later on because the results of the first participants showed that too many mothers were included in the screening step 2 showing no current mental health problems. To increase the response among the major groups of parents with a migration background, all study documents of the screening step 1 were translated to English, Turkish, and Arabic.

#### Screening step 2

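### Stressors that earn points towards the step 1 cut-off are also analysed as risk factors, so their odds ratios for mental disorders are biased by selection

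*Protocol article*

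**What the plan says.** All references are to the protocol article.

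- **Step 1 content (Instruments).** The health questions include "lack of impulse control or mood swings, pre-existing mental health disorders". Further questions cover "stress related to relationships, family and work, lack of social support and critical life events related to the pregnancy and child".
- **Scoring (Instruments).** "We developed a scoring system with points ranging from 0–5 for each question".
- **Selection (Procedures, Preliminary results).** Mothers with 10 points or more are positive. Only they go on to step 2, where the MINI, EPDS and PBA are given. No interviewed subsample of screen-negative mothers is described.
- **Determinants (Endpoints).** The factors to be examined are given as "Potential risk and protective factors such as sociodemographic characteristics, marital, family, health, and work related stressors, critical life events, and pre-existing mental health disorders".
- **Model (Statistical analysis).** "Influencing factors for the presence of psychosocial stress or mental health disorders are analysed using logistic regression". Missing values are left as they are, and each analysis uses the data available for it. The regression sample is not named. The precision calculation for occurrence uses 1200 cases over all 6000 participants.
- **Psychosocial stress.** It has no entry among the endpoints. The Abstract treats step 1 positives as mothers showing signs of it, Table 1 lists no other stress instrument, and the Discussion presents the step 1 questionnaire as a screening tool for it that contains known stressors.

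**The concern.** The determinants and the selection score share items. A mother with a scored stressor needs fewer symptom points to reach 10 than a mother without it. Exposure therefore affects whether the disorder outcome is observed at all, separately from any effect on the disorder.

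For psychosocial stress the problem is more direct if the outcome is the total score dichotomised at 10, because the factor then adds points to its own outcome.

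Objective (ii), on risk and protective factors, is at stake. The Discussion expects known determinants to be replicated. A scored stressor could appear as a determinant of stress because it was scored, while a real association with a diagnosed disorder could be weakened, lost or exaggerated depending on the regression sample.

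**Working it through.** **1. The article's own figures.** The exact Clopper-Pearson interval for 1200/6000 is 18.99% to 21.03%, which matches the stated 19% to 21%. The positive rate in mothers is 1139/4719 = 24.1%, as stated. No figure is given for the regressions.

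**2. Inputs.** From the article: cut-off 10, items scored 0–5, 24.1% positive, planning prevalence of disorder 20%.

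Assumed, because the article does not give them:
- a binary factor present in 25% of mothers and carrying k = 0, 1, 3 or 5 points;
- all other points negative binomial (shape 4), with mean μ without disorder and μ+4 or μ+8 with disorder, independent of the factor given disorder;
- μ set so that 24.1% of mothers reach 10;
- every positive mother completes step 2.

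**3. Formulas.** For exposure x (0 or 1), let p_x be the probability of disorder, a_x the probability of a positive screen with disorder, and b_x the same without disorder. Write odds(u) = u/(1−u).

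- Within step 2: OR = true OR × (a_1/b_1) / (a_0/b_0)
- Screen-negatives as non-cases: OR = odds(p_1·a_1) / odds(p_0·a_0)
- Score ≥10 as outcome: OR = odds(q_1) / odds(q_0), with q_x = p_x·a_x + (1−p_x)·b_x

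Points for the factor raise both a_1 and b_1. In this model they raise b_1 proportionally more, because mothers without disorder start further below the cut-off. Hence the first ratio falls and the second rises.

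**4. One case in full.** True OR 1.0, k = 3, shift 4, so p_0 = p_1 = 0.20 and calibration gives μ = 5.47. Unexposed mothers need 10 other points: b_0 = 0.1307, a_0 = 0.4301. Exposed mothers need 7: b_1 = 0.3278, a_1 = 0.6577.

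- Within step 2: (0.6577/0.3278) / (0.4301/0.1307) = 2.006/3.291 = 0.61
- Negatives as non-cases: odds(0.1315)/odds(0.0860) = 0.1515/0.0941 = 1.61
- Score ≥10: q_1 = 0.3938, q_0 = 0.1906; odds 0.650/0.235 = 2.76
- Check: 0.25 × 0.3938 + 0.75 × 0.1906 = 0.241

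A simulation of one million mothers gives 0.60, 1.59 and 2.77 for this case.

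**5. Range.** Simulated odds ratios over the two shifts:

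| True OR | Points k | Within step 2 | Negatives as non-cases | Score ≥10 |
|---|---|---|---|---|
| 1.0 | 0 | 0.98–1.00 | 0.99 | 1.00 |
| 1.0 | 1 | 0.79–0.85 | 1.11–1.16 | 1.31–1.36 |
| 1.0 | 3 | 0.44–0.60 | 1.35–1.59 | 2.40–2.77 |
| 1.0 | 5 | 0.21–0.39 | 1.62–2.25 | 4.87–6.53 |
| 2.0 | 0 | 2.01–2.02 | 1.83–1.88 | 1.21–1.39 |
| 2.0 | 1 | 1.57–1.70 | 2.10–2.11 | 1.63–1.81 |
| 2.0 | 3 | 0.88–1.19 | 2.55–2.95 | 3.26–3.30 |
| 2.0 | 5 | 0.41–0.77 | 3.12–4.26 | 6.73–7.88 |

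For true OR 1.0, taking the factor's own points out of the score returns the last column to 0.99–1.00, so the scoring is the cause. At k = 0 the step 2 estimate is undistorted. The mild attenuation to 1.83–1.88 in the fourth column comes from cases the screen misses, not from scoring.

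**The case against.** **The stress outcome is not defined as score ≥10.** This stands. The reading is inferred from the Abstract, Table 1 and the Discussion. Stress is not a listed endpoint, and an outcome built from symptom items alone would remove the built-in inflation. That definition may sit in a document not shown. A reader might infer that all odds ratios for stress are inflated by construction; the article supports this only conditionally.

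**Not every determinant scores.** This also stands. The item key is not shown. Age, social status or migration status may carry 0 points, and childhood trauma is asked only in step 2. A reader might conclude that objective (ii) fails as a whole, but the scoring problem is shown only for factors that carry points.

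**The sizes rest on assumptions.** True. At 1 point the bias is modest. The direction within step 2 or with negatives as non-cases does not depend on the exact weight.

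**The available-data rule already excludes unassessed mothers.** That is the natural reading for the regressions, and it leads to the downward bias. The 1200-of-6000 denominator belongs to the occurrence estimate, but it shows how the other coding could enter.

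**The analysis is exploratory.** The article states: "All CIs and *p* values are two-sided and are interpreted exploratively (there is no formal significance level". This governs how p values are read and does not remove bias from an estimate. The Discussion promises to consider types of bias, but names recruitment, education and maternal report, not this one.

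**Could mothers interviewed below 10 points rescue the estimate?** The article says the score was adjusted during the study, and a reader might infer that such mothers exist. It does not say whether 10 is the earlier or the later value, so no such group is established and a verification-weighted analysis cannot be built on it.

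**Conclusion.** The point holds for factors that carry step 1 points. Their disorder odds ratios are biased downward within step 2 and upward if unassessed screen-negatives are coded as non-cases. The article fixes the scoring, the selection and the regression, and mentions no correction. If psychosocial stress is the total score at 10 or more, scored factors are also inflated there.

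The figures in the working illustrate possible size and are not estimates for this study. With a true odds ratio of 2.0 and 3 points, the step 2 result is 0.88–1.19, so a real risk factor could disappear; whether any does depends on weights that are not shown. Factors with 0 points and no other link to the score are not distorted within step 2.

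**What to change.** Add to the Statistical analysis section:

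1. Psychosocial stress is modelled in the full step 1 sample with an outcome that leaves out the exposure items: the PHQ-4, which the article names among the step 1 sources, or a symptom-only sub-score without the stressor, life-event and pre-existing-disorder items. The total score at ≥10 is not used as the outcome.
2. Mothers without step 2 data are not coded as non-cases in the regressions.
3. Odds ratios for MINI, EPDS and PBA outcomes are reported as conditional on a positive screen. For items that score in step 1 they are not presented as population risk or protective factors.

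No new data are needed. The cost is in interpretation: the full-sample determinant model describes symptoms, not diagnoses. The third change discloses the selection bias without removing it, and factors that score 0 but are related to the score in other ways can still be affected, so the conditional label should cover all disorder odds ratios.

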## Preliminary results

By mid-March 2020 29,516 of the potential study participants received at least an invitation letter and at least one reminder. Overall, 4719 mothers and 889 fathers completed the screening step 1. Three participants were adoptive parents and three participants did indicate to be other caregivers (for example stepparents). So far, either the mother or the father or both parents of 4866 children (16.5%) have completed the screening step 1 questionnaire. All persons gave their informed consent prior to their inclusion in the study.

4472 participants came from Berlin, 75 from Flensburg, 933 from Leipzig and the remaining participants were living elsewhere at the time of the screening step 1. 811 participants were younger than 30 years, 4779 between 30 and 49 years and 21 participants 50 years or older (three values missing). 860 participants did indicate to be born outside Germany, 272 to be single parents and 2351 participants having more than one child.

Overall, 1139 mothers (24.1%) and 154 fathers (17.3%) screened so far “positive” in the screening step 1. As described above, only mothers with a “positive” screening step 1 are invited to the screening step 2.

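### Cost comparisons by linear regression or ANCOVA need robust or bootstrap intervals: the usual single-variance intervals will be too narrow for a small costly group and too wide for a large one

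*Protocol article*

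**What the plan says.** The Statistical analysis section of the protocol article names the method and gives costs as its example: "Influencing factors or group comparisons for continuous variables (e.g. costs) will be analysed by linear regression or analysis of covariance (ANCOVA". Results are to be presented as coefficients or mean values, each with a 95% interval and a p value. The section mentions no robust variance, bootstrap, transformation or generalised linear model for costs. On interpretation it says "All CIs and *p* values are two-sided and are interpreted exploratively (there is no formal significance level".

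The same section builds each cost by "multiplying the frequency of utilization and corresponding standardized cost rates". The Endpoints section lists utilisation and costs as secondary and includes "acute and rehabilitation hospital stays, utilisation of Early Childhood Intervention program components" among the items.

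Detailed utilisation is collected from screening step 2 onward. On numbers, the plan says "about 1,500 of the estimated 6,000 mother–child-pairs are expected to be included into the screening step 2", and of these "we estimate that about 1,200 participating mother–child-pairs with maternal mental health disorders and/or symptoms of regulatory problems in the child will be identified". The Preliminary results section reports that "1139 mothers (24.1%) and 154 fathers (17.3%) screened so far" positive.

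**The concern.** A cost formed as frequency times unit rate cannot be negative. Most families will have modest values, and a few hospital or rehabilitation stays can dominate a group total. For such data, a group with a higher mean normally has a larger variance as well.

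Standard linear regression and ANCOVA estimate one residual variance for everybody. When groups are unequal in size and in variance, the pooled estimate is driven by the larger group. The interval for the difference is then too short if the smaller group is the more variable one, and too long if the larger group is.

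At stake is the stated precision for objective (iii), the use and cost of services. No significance level is set, so readers will rely on the intervals themselves.

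**Working it through.** **The plan's own precision figure.** The exact Clopper-Pearson interval for 1,200 of 6,000 is 18.99% to 21.03%, which matches the stated 19% to 21%. This is the only precision figure in the article. It concerns prevalence, and there is none for costs.

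**Inputs.** From the article: about 1,500 pairs in step 2, of which about 1,200 are affected (1,200/1,500 = 80%), and 1,139 mothers screening positive so far. Not in the article, so assumed: the share p of the costlier group (10–30% for a small group, 50%, and 80% for the planned affected majority), and the ratio k of its cost SD to that of the rest (1 to 3).

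**Formula.** Take a two-group comparison in N pairs and set the SD of the rest to 1.

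- SE² from the pooled variance: [p·k² + (1 − p)] / [N·p·(1 − p)]
- True SE²: k²/(N·p) + 1/(N·(1 − p)) = [k²·(1 − p) + p] / [N·p·(1 − p)]
- Ratio of pooled to true SE: R = √{[p·k² + 1 − p] / [k²·(1 − p) + p]}
- Coverage of a nominal 95% interval: 2Φ(1.96·R) − 1

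N cancels, so a larger sample with the same shares does not help.

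**Two examples.**

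- p = 0.10, k = 2: R = √(1.3/3.7) = 0.593. Then 1.96 × 0.593 = 1.162, and coverage is 75%.
- p = 0.80, k = 2: R = √(3.4/1.6) = 1.458. Then 1.96 × 1.458 = 2.857, and coverage is 99.6%.

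**Coverage of nominal 95% single-variance intervals, by share of the costlier group.**

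| SD ratio k | 10% | 20% | 30% | 50% | 80% |
|---|---|---|---|---|---|
| 1 | 95% | 95% | 95% | 95% | 95% |
| 1.3 | 89% | 91% | 92% | 95% | 98% |
| 2 | 75% | 82% | 88% | 95% | >99% |
| 2.3 | 71% | 80% | 86% | 95% | >99% |
| 3 | 64% | 75% | 84% | 95% | >99% |

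**Check with skewed costs.** Lognormal and gamma costs were simulated with a coefficient of variation of 1 or 2, N = 1,500 and 4,000 runs per setting. The mean and SD ratios were equal.

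- Costlier group of 150: coverage 75–76% at ratio 2 and 63–65% at ratio 3.
- Costlier group of 300: 80–82% and 74–76%.
- Equal means and SDs, groups of 150 or 300: 94–96%, so skewness alone does little harm here.
- Equal group sizes: 93–96%.
- Costlier group of 1,200: 99–100%.

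At ratio 1.3, simulated coverage for a group of 10–30% was about 90–93%, within about a point of the formula.

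**After allowing unequal variances.** On the same simulated data at ratios 2–3, unequal-variance (Welch) intervals cover 90–95% for a group of 150, 92–95% for 300 and 84–93% for 30. In a two-group comparison the HC3 variance of a group mean is s²/(n − 1), against s²/n for Welch, so HC3 intervals are marginally wider and these figures approximate them.

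**The case against.** The strongest reply is that the article never says how standard errors are computed. Robust or bootstrap intervals are compatible with its wording, and an analysis plan that is not shown may specify them. This stands as a limit: the point depends on reading the unqualified terms in their usual sense. It does not remove the point, because the article itself fixes the method for costs and attaches 95% CIs and p values to it without qualification.

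Second, a reader might infer that all cost intervals under objective (iii) would be much too narrow. The documents do not support that. The only split of step 2 that the article gives is about 1,200 affected of 1,500, and there a costlier majority makes the intervals too wide. Nor does the article plan cost comparisons by single disorder: the Endpoints section lists single disorders as outcomes of presence, separately from costs. Small groups are plausible, since the Discussion wants utilisation behaviour by subgroup, but their sizes are assumed here.

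Third, a reader might infer that linear regression is the wrong model for skewed costs. That also goes too far. It targets the arithmetic mean cost, which is the relevant quantity, and with equal SDs its coverage stays near 95% despite the skew. Preferring a gamma or two-part model is a matter of judgement.

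Finally, costs are secondary and all inference is exploratory. This limits the consequence, but an interval labelled 95% should still have roughly that coverage.

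**Conclusion.** The concern holds in a limited form. Under the usual single-variance reading, cost intervals will be miscalibrated whenever group sizes and cost variances both differ, and the direction depends on which group is more variable.

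For a costlier group of 10–30%, coverage falls to about 89–93% at an SD ratio of 1.3, 75–88% at 2 and 64–86% at 2.3–3. It is about 95% with equal SDs or equal group sizes, and 98% or more when the costlier group is the 80% majority. These figures rest on assumed SD ratios and group shares, because the article reports nothing about the cost distribution. The cause is larger variance in the smaller group, not skewness as such.

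The result would be misleading precision in exploratory, secondary cost results. No primary endpoint is affected.

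**What to change.** Keep linear regression or ANCOVA on arithmetic mean costs. Add one sentence to the Statistical analysis section stating that CIs and p values for cost outcomes use heteroscedasticity-robust (HC3) standard errors or a non-parametric bootstrap. A gamma model with log link, or a two-part model if there are many zeros, can be named as an optional sensitivity analysis.

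The cost is a few lines of code and no new data. Intervals will widen for small costly groups and narrow where the costlier group is the majority. The fix is incomplete in very small groups. With 30 pairs, unequal-variance coverage was 84–93% at ratios 2–3. With equal SDs it was 84–94%, against 95–96% for the single-variance interval. Cost contrasts involving groups of that size should therefore be reported with an explicit caution.

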Overall, more population-based epidemiological data on mental health in early childhood as well as information on health and social care service utilisation are needed to clarify the situation in Germany.

The collaborative German *SKKIPPI* project would like to make a contribution to this and includes an observational population-based cohort study as well as two interventional studies (https://skkippi.ipu-berlin.de/). The SKKIPPI intervention studies are randomized controlled trials (RCT) that will evaluate the efficacy of a specific parent-infant/toddler psychotherapy (6 week program according to a specific SKKIPPI Study Treatment Manual) compared to care-as-usual in mothers with mental health disorders and in mothers of children with regulatory problems, respectively. The two RCTs will be performed in Berlin (both RCTs), Flensburg (only RCT for mother with mental health disorders) and Leipzig (only RCT for mothers with children with regulatory problems), so within the same cities as the cohort study, but they will be described separately. Participants of the cohort study, which qualify for the interventional studies, are invited to take part in the RCTs. If they agree to participate, they will be excluded from the follow up assessment of the cohort study. SKKIPPI is performed within and funded by the German Health Care Innovation Fund, aiming at improving quality and integration of health care [54]. The present article focuses on the rationale, objectives, and design of the observational population-based cohort study as part of the SKKIPPI project.

The primary aim of the SKKIPPI cohort study is to assess the occurrence and course of psychosocial stress and mental health disorders in parents and their children in early childhood in three German regions. Furthermore, potential risk and protective factors as well as the use of health care and social service related to these disorders will be examined.

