**Fig. 1 Fig1:**
[figure not shown]
Flowchart SKKIPPI Cohort Study

While both mothers and fathers can participate in the first step, for the second step, only mothers will be included. As mothers are usually the main reference persons of the children in the first years of life, a significantly higher participation of them is expected. For this reason, we decided to assess mental health problems only in mothers and their children. Mothers who screened “positive” in the first step, meaning achieved at least 10 points in the online questionnaire, will enter the second step of the screening for a more in-depth assessment, where specially trained study staff will conduct phone interviews for mental health disorders (adapted version from the MINI [59]). In addition, questions on depressive symptoms, symptoms of parental burnout, symptoms of regulatory problems of the children, questions on childhood trauma of the parents, and detailed data on kind and frequency of health and social care utilisation will be collected (via telephone interview or online questionnaire).

After 6 months, a follow-up assessment will be performed with all mothers with a current mental health disorder (based on the MINI interview [59]) or a positive outcome in the Edinburgh Postnatal Depression Scale (EPDS) [5] or Parental Burnout Assessment questionnaire (PBA) [12] within the screening step 2 (“positive” screening step 2). The same data as in the screening step 2 stage will be collected, with additional data about the use of health care services and official support services in the last 6 months. We estimated that 80% of the participants would take part in the follow-up assessment.

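### The available-case rule leaves baseline occurrence open to selection bias from step-2 non-participation, and the 6-month course open to selection bias from follow-up loss and RCT exit

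*Protocol article*

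**What the plan says.** The Statistical analysis section sets one rule for every analysis: "Missing values are not replaced. All analyses are carried out with the respective available data (full analysis set"). It names no weighting, imputation or sensitivity analysis.

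Three features of the design determine what that rule leaves out:

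- **Entry to step 2.** Preliminary results states that "only mothers with a “positive” screening step 1 are invited to the screening step 2". Entry is by invitation, so a mother can decline. The article gives no refusal rate and no rule for counting those who decline.
- **Follow-up participation.** Procedures says: "We estimated that 80% of the participants would take part in the follow-up assessment".
- **RCT exit.** The Rationale says of cohort mothers who qualify for the intervention trials: "If they agree to participate, they will be excluded from the follow up assessment of the cohort study".

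The planning figures are in the Statistical analysis section. From 6,000 participating pairs, "about 1,500 of the estimated 6,000 mother–child-pairs are expected to be included into the screening step 2", and then "we estimate that about 1,200 participating mother–child-pairs with maternal mental health disorders and/or symptoms of regulatory problems in the child will be identified". The precision statement takes 1,200 of 6,000 as the occurrence.

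Under Strengths and potential limitations, the article promises to consider possible types of bias when results are interpreted. It attaches no analysis to that promise.

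**The concern.** Occurrence and course are together the primary aim given in the Rationale. Each rests on a group that has already been filtered, and the rule takes what remains as it stands.

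For occurrence, the filter acts on one stratum only. Step-1 negatives are never interviewed, and the precision statement treats them as non-cases. They therefore all stay in the denominator, while positives who decline the interview drop out. The pooled proportion falls even when those who decline are just like those who accept.

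For the course, the filter has two parts: ordinary loss by 6 months, and removal of mothers who join an RCT. The RCTs take mothers with mental health disorders and mothers of children with regulatory problems, so their entrants are not a random part of the cohort. If unseen mothers have a different course, available-case results describe only the remainder.

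The article gives its own reasons to expect selective participation. It says a psychiatric interview may distress participants, names stigma as a barrier to care, and expects socially disadvantaged parents to be under-represented.

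**Working it through.** **Inputs from the Statistical analysis section:** 6,000 mothers; 1,500 step-1 positives, so 4,500 negatives; 1,200 cases, all among the positives. I read 1,200 as the number found if all 1,500 are interviewed. The article does not say whether the step from 1,500 to 1,200 already allows for refusal.

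**Input from Preliminary results:** 1,139/4,719 = 24.1% of mothers screened positive, close to the planned 1,500/6,000 = 25%.

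**Input from Procedures:** 80% follow-up participation.

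**Assumed, because the article gives no figure:** step-2 refusal r of 10% to 40%; RCT share of 0%, 10% or 20%; a 10-point difference in outcome rate between seen and unseen mothers.

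**1. The plan's own interval.** Clopper-Pearson limits for 1,200/6,000 are 18.99% and 21.03%. The stated interval of 19% to 21% reproduces. It presumes that all 6,000 mothers are classified.

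**2. Occurrence when refusal is random among step-1 positives.**

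Available-case estimate = 1,200(1 − r) / [4,500 + 1,500(1 − r)]

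| r | Cases / classified | Estimate | 95% CI |
|---|---|---|---|
| 0% | 1,200 / 6,000 | 20.0% | 19.0% to 21.0% |
| 10% | 1,080 / 5,850 | 18.5% | 17.5% to 19.5% |
| 20% | 960 / 5,700 | 16.8% | 15.9% to 17.8% |
| 30% | 840 / 5,550 | 15.1% | 14.2% to 16.1% |
| 40% | 720 / 5,400 | 13.3% | 12.4% to 14.3% |

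Keeping refusers in the denominator as non-cases does not help: at r = 20% it gives 960/6,000 = 16.0%.

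Reweighting interviewed mothers to all step-1 positives gives (1,500/6,000) × (960/1,200) = 0.25 × 0.80 = 20.0%. The result is the same for every r in the table.

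**3. Occurrence when refusal also depends on the outcome** (overall refusal 20%).

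- Cases refuse at 25%, non-cases at 0%: available cases 900/5,700 = 15.8%; reweighted 0.25 × 900/1,200 = 18.8%.
- Cases refuse at 15%, non-cases at 40%: available cases 1,020/5,700 = 17.9%; reweighted 0.25 × 1,020/1,200 = 21.3%.

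Reweighting by step-1 result alone leaves an error here, but a smaller one.

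**4. Precision cost of reweighting at r = 20%** (normal approximation).

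Variance = 0.25² × 0.8 × 0.2/1,200 + 0.8² × 0.25 × 0.75/6,000 = 0.0000083 + 0.0000200 = 0.0000283. The half-width is 1.96 × √0.0000283 = 1.04 points. With all 1,500 interviewed it is 1.96 × √(0.2 × 0.8/6,000) = 1.01 points.

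**5. Six-month course.** I use 1,200 as a rough guide only. Follow-up eligibility in Procedures (MINI, EPDS or PBA) is not the same group, since a child's regulatory problem alone does not qualify. The scenarios let RCT entrants leave first and apply the 80% to the rest.

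Bias = share unseen × difference between seen and unseen

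| RCT share | Seen | Share unseen | Bias at 10 points | CI half-width at a 50% rate |
|---|---|---|---|---|
| 0% | 1,200 × 0.8 = 960 | 20% | 2.0 points | 3.2 points |
| 10% | 1,080 × 0.8 = 864 | 28% | 2.8 points | 3.4 points |
| 20% | 960 × 0.8 = 768 | 36% | 3.6 points | 3.6 points |

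With no difference between seen and unseen mothers, the bias is zero in every row.

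**The case against.** The strongest reply is that no bias has been shown. The article gives no refusal rate, no RCT share and no difference between seen and unseen mothers. All analyses are called exploratory, possible bias is to be considered at interpretation, and weighting models often sit in an analysis plan that is not shown here. Much of this stands, and it limits what can be said. It does not remove the point, because the article does not leave the matter open: it fixes an available-case rule for all analyses.

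Several stronger readings are tempting, and the documents do not support them:

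- *The 6-month course is biased.* A reader might infer this from the 20% loss and the RCT exclusion. Only the exposure is documented, and the two losses could act in opposite directions.
- *Follow-up loss and RCT exit distort baseline occurrence.* Both follow step 2, and these mothers keep their step-2 data. Only step-2 non-participation bears on occurrence.
- *The 80% ignores RCT entrants.* The sentence does not say whether they fall within the 20%, in addition to it, or outside its base.
- *RCT exit is simply missing data.* It is a disclosed design rule. Entrants are randomised to study therapy or care-as-usual, so whether their course belongs in the result is partly a question of target population.
- *The flow chart omits these mothers.* The figure is not available, so this cannot be judged.

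Two more limits stand. Available-case regression for risk factors can be valid when missingness depends only on covariates in the model, so the point concerns occurrence and course. That the collected data predict participation is plausible but not documented.

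**Conclusion.** The point holds as an exposure to selection bias created by a stated rule.

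For occurrence the mechanism needs no difference between refusers and participants. It needs only some refusal in step 2, step-1 negatives counted as non-cases (as the plan's own interval does), and a pooled available-case proportion. An assumed 10% to 20% refusal then moves the planned 20% to between 18.5% and 16.8%. At 20% refusal the whole interval lies below the planned 19% to 21%. The refusal rate itself is inferred as possible from the invitation and is not stated.

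For the 6-month course, size and direction are unknown. The 2.0 to 3.6 points above depend on an assumed 10-point difference and assumed RCT shares. They are somewhat below, or equal to, the sampling half-width.

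The sponsor should change the rule, since following it can give a wrong occurrence and the data for a better estimate are already planned.

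**What to change.** Replace the available-case sentence in the Statistical analysis section with the following:

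- **Occurrence.** Weight step-2 participants to all step-1 positives, or multiply impute step-2 outcomes for positives not interviewed. Use the step-1 score, symptom items and sociodemographic data. State how step-1 positives without an interview enter numerator and denominator.
- **Six-month course.** Give estimates with inverse-probability weights or multiple imputation based on step-1 and step-2 data, alongside the available-case analysis.
- **RCT entrants.** State whether the target population for the 6-month course includes mothers who enter the RCTs, and whether the 80% counts them. Report their number and step-2 characteristics separately.

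The cost is modest analysis work and slightly wider intervals: for occurrence at 20% refusal, about 1.04 against 1.01 points of half-width. No new data are needed. Neither method corrects refusal or loss driven by factors that were not measured, so the promised discussion of bias at interpretation is still needed.
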